## Data collection and analyses

### Assessors and details of blinding

Assessors will be occupational therapists or physiotherapists blinded to the treatment group of the child. Each assessor will be trained by a chief investigator in reliable administration of all measures and provided with a study assessment protocol to ensure consistency of assessment techniques between assessors. Multiple efforts will be made to retain blinded status of assessors. Treating therapists, research personnel, child-participants and families will be routinely reminded that it is critical that blinding of the assessor is retained and the assessor will remind the family of this on initial contact at each assessment. Study numbers allocated to children will not contain a fixed code denoting intervention group. The success of blinding will not be measured as methodological experts argue against such practice [28]. Therapists providing the WHO are unable to be blinded to treatment group and hence may adjust co-interventions differently in the two groups. Measurement of co-interventions and comparisons between groups is therefore is an important part of this trial. Blinding of parents and participants to intervention group is not possible.

### Demographic and diagnostic characteristics

Consistent with best practice in CP [1], the severity of CP will be assessed and classified at baseline using the Gross Motor Function Classification System [29], Manual Ability Classification System [23], Communication Function Classification System [30] and Bimanual Fine Motor Function scale [31]. In addition, the type of movement disorder (that is, spastic or mixed) and severity of spasticity in the included upper limb(s) will be rated using the Hypertonia Assessment Tool [32] and the Australian Spasticity Assessment Scale [33, 34] respectively. Information from these tools will help to describe the characteristics of the study sample and be used in post-hoc analyses of outcomes. A study specific questionnaire will measure a range of demographic and other variables including age, gender, associated conditions (intellectual disability, sensory impairments), family configuration, range of services received and socio-economic status as defined using the Socio-Economic Index for Areas data [35].

### Outcome measures

The primary outcome measure is passive range of wrist extension (measured with the fingers extended). Range of wrist movement is operationalised from -70° (full wrist flexion) to + 80° (full wrist extension) where 0° indicates a neutral position. Range of movement will be measured using a goniometer for extension/flexion movements, an inclinometer for supination/pronation and inertial motion sensors. Inertial motion sensors, constructed specifically for the trial, will be used to measure active and passive wrist extension, with fingers extended as well as functional range of wrist extension elicited during standardised tasks. Other measures across the domains of the ICF will also be used to evaluate the effect of the intervention. Table 2 displays each variable, the measurement tool selected and provides an overview of psychometric evidence for the selected tools.

**Table 2 Tab2:** Variables and outcome measures

Variable	Measurement tool	Additional information
ICF level: Body function: baseline, 6, 12, 18, 24, 30, 36 months		
Passive range of motion: elbow extension, wrist extension (with fingers extended), wrist extension (with fingers flexed), supination	Standardised goniometric measurement; inclinometer for measures of supination;	Goniometric measurements have a high level of intra-rater reliability when measuring passive range of movement in the lower limb in children with CP (ICC >.80) and SEM of 3.5° [44, 45].
	Inertial Motion sensors.	Inertial motion sensors (see additional information below) will be used to measure passive wrist extension with fingers extended only.
Active range of movement: elbow extension, wrist extension (with fingers extended), wrist extension (with fingers flexed), supination	Standardised goniometric measurement and use of inclinometer for measures of supination.	See additional information above.
	Inertial Motion sensors	Inertial motion sensors (see additional information below) will be used to measure active wrist extension with fingers extended only.
Functional range of wrist extension during standardised tasks.	Inertial Motion sensors.	A wireless inertial motion sensor for children has been designed and engineered for this trial to measure wrist flexion/extension movement during functional activity. The sensors use a combination of inertial sensor technologies to provide an accurate estimate of orientation referenced to a fixed frame [46]. Once correctly positioned they wirelessly capture movement with 3° of freedom in a virtual reality environment to provide continuous kinematic data during unrestricted functional movements. The validity and reliability of the newly developed sensor has been assessed with 10 children with CP (aged 4–12 years) against 3DMA, the ‘gold standard’ method to quantify movement. Preliminary data demonstrates the inertial motion sensors have excellent static and dynamic accuracy (+/-0.5 and +/-1.2° respectively).
Muscle stiffness (finger flexors, wrist flexors, pronators and elbow flexors)	Modified Ashworth Scale [47]	The six point Modified Ashworth Scale has moderate intra-rater reliability when assessing the elbow (ICC 0.66) and wrist flexors (ICC 0.57) in children with CP [48].
Muscle spasticity (finger flexors, wrist flexors, pronators and elbow flexors)	Modified Tardieu Scale [47]	The Modified Tardieu Scale has moderate to high intra-rater reliability when assessing the elbow (ICC 0.65) and wrist flexors (ICC 0.92) in children with CP [48].
	Australian Spasticity Scale [33]	The Australian Spasticity Assessment Scale has demonstrated moderate to high inter-rater agreement (47–100 %) [33]
Grip strength	Hand held dynamometer (CITEC)	Dynamometery has been shown to have excellent levels of inter-rater (ICC 0.95) and test-re-test reliability (ICC 0.96) when measuring strength in the hand of children with hemiplegic CP [49].
Hand deformity	Neurological Hand Deformity Classification Scale [50]	The Neurological Hand Deformity Classification has evidence of reliability for children with spastic cerebral palsy with high inter-rater agreement (Kappa 0.87) and intra-rater agreement (Kappa 0.91) [15]
Thumb position	House Thumb in Palm classification [51]	This measure has been developed for children with CP based on the predictors of surgical success and has been found to be reliable: Kappa = 0.73 (rater agreement) and 0.74 (test-re-test agreement) [49, 52].
Hand pain	Study specific questionnaire	The study specific questionnaire was developed for this study to document parent perception of domains unable to be captured in existing measures. Questions will be completed by the child where possible or by a parent/carer proxy. Although proxy respondents are known to underestimate pain, parent-reported pain will be required for children who are more severely cognitively impaired or unable to communicate their pain effectively.
Activity domain of the ICF: baseline, 12, 24 & 36 months		
Self-care skills	Pediatric Evaluation of Disability Inventory – Computer Adaptive Test [53]	This is a standardised assessment of how children with impairments function in the context of their daily life. The Pediatric Evaluation of Disability- Computer Aided Test provides an accurate and precise assessment of abilities in four functional domains (ICC 0.99). For this trial only data from the Daily Activities domain will be collected.
Manual ability	ABILHAND-Kids [54]	This tool has been Rasch analysed and has demonstrated validity and appropriate range and measurement precision for clinical practice and research: reliability: *R* = 0.94; reproducibility over time: *R* = 0.91 [54].
Speed and dexterity	Box and Blocks Test [55]	This test has a high level of intra-rater (ICC 0.99) and test-retest reliability (ICC 0.85) [56].
Hand function	Modified House Scale [57]	This scale is reliable in children with CP: inter rater reliability (ICC 0.94-0.96); intra rater reliability (ICC 0.93-0.96) [57]. Rasch analysis was performed on the original scale and the items reduced: analysis suggests that the modified version demonstrates good construct validity [58].
Ease of care-giving	Study specific questionnaire	Parent response to specific questions regarding the child’s ability to use their hands in self-care tasks or, for children with severe forms of cerebral palsy the ease with which parents or carer’s can complete daily tasks of care for them.
Participation domain of ICF: Baseline & 3 years only		
Participation	Participation and Environment Measure-Child & Youth [59]	Designed to measure frequency of participation, involvement during participation and the impact of the environment on participation in children aged 5 to17 years [59]. This measure captures participation outcomes in home, school and community contexts. Reliability of the frequency scales (ICC range 0.58-0.84) and involvement scales (ICC 0.69-0.76 is moderate to high [59].
Child Health related quality of life and care-giving burden	Cerebral Palsy Quality of Life Questionnaire – Child and Teen versions [60, 61]	Due to the varying ages and abilities of the child-participants, both parent- and self-report versions of the Child or Teen CP Quality of Life will be used to measure quality of life. Test-re-test reliability for the Child version was high (ranged from ICC 0.76 to 0.89 across 7 scales) [61], and moderate to high for the Teen version (ICC 0.57 to 0.88) [60]
Health economic measures: Baseline, 12, 24, 36 months		
Cost Effectiveness Analysis (CEA)	Study specific questionnaire	Data on type and number of health professional appointments attended by child in preceding 6-month time period will be utilised for calculation of healthcare cost as well as out of pocket costs to families. Net incremental costs expressed as ICER to meaningful clinical and physical outcomes (e.g. selected from body function domains; activity domains; and the clinical quality of life questionnaire).
Cost Utility Analysis (CUA)	Child Health Utility -9 Dimensions [37]	Net ICER to the quality of life improvement for children and parents/carers expressed as QALY using an economic MAUI. Where possible the Child Health Utility will be completed along with the parent proxy version. The Child Health Utility has 9 items, takes 2-3 min to complete and covers worry, sadness, pain, tiredness, annoyance, school work, sleep, daily routine and ability to join in activities. The Child Health Utility-9D demonstrated good validity and high levels of agreement with a similar instrument (ICC: 0.742) [62]. The parent measure of quality of life, the Assessment of Quality of Life 8 Dimensions has high reliability (ICC 0.89) [36].
	Assessment of Quality of Life 8 Dimensions [36]	
Cost Consequences Analysis (CCA)		CEA/CUA reported alongside a broader documentation of child & family relevant outcomes

Note: *ICC* intraclass correlation coefficient, *SEM* standard error of measurement, *3DMA* three dimensional motion analysis, *ICER* Incremental Costs Effectiveness Ratio, *MAUI* multi-attribute health utility instruments, *QALY* quality adjusted life year, *CEA* Cost effectiveness analysis, *CUA* Cost utility analysis

### Economic analysis

Economic analysis in the context of trials is designed to answer one or both of two questions: i) does the treatment being evaluated offer value-for-money (i.e. ‘allocative efficiency’); and ii) if so, how best to design/implement it (i.e. ‘technical efficiency’). In this trial we are focussed on technical efficiency. Specifically, is the care pathway more cost-effective with the addition of a WHO for children with CP than without? Economic methods have been chosen therefore to focus on appraisal using trial-based data (with limited economic modelling) and to deal with variability in usual multidisciplinary care. A comprehensive analysis of usual care activities will enable: i) specification of a weighted average usual care pathway (i.e. weighted by activity prevalence); ii) incremental cost-effectiveness ratios (ICERs) presented by state/site, as well as by overall trial results; and iii) extensive sensitivity/uncertainty analyses to detail cost and outcome drivers.

The technical efficiency focus will make cost-effectiveness analysis (CEA) and cost consequences analysis (CCA) the primary analysis, with ICERs that focus on body function, activity measures and child/family quality of life and health utility outcomes from both health sector and service funder perspectives. The key trial-based ICERs are: i) the ‘net cost per 10° improvement in passive range of movement at 3 years’; ii) the ‘net cost per unit of improvement on the *Cerebral Palsy-Quality of Life’* measure; iii) the ‘net cost per *Adult Quality of Life-8 Dimensions’* [36] improvement for parent/carer; and iv) the ‘net cost per *Child Health Utility 9D’* [37] improvements for children. While economic quality of life instruments are usually focussed on value-for-money comparisons, the difficulties in modelling longer term outcomes in this trial, leads to their primary purpose being to help establish technical efficiency. ICERs will be reported as both point and range estimates. In the CCA, ICERs will be reported and interpreted alongside the full range of body function and activity measures collected. A Cost-Utility Analysis (CUA) with variable time horizons and best available data will be included in sensitivity analysis against a specified decision threshold (i.e. < $50,000 per QALY). In addition to the CEA/CCA and CUA, a broader economic approach will be undertaken to capture policy and implementation/policy issues (e.g. acceptability to stakeholders, equity impacts, feasibility of implementation, quality of the evidence base) using ***A***ssessment of ***C***ost ***E***ffectiveness (*ACE*) methods. *ACE* has been used across a series of commissioned and NHMRC-funded projects [38].

Costs will be calculated using pathway analysis to document treatment activity, specify unit prices and estimate costs and potential cost offsets across the study groups. For usual multidisciplinary care, a number of pathways will be constructed and analysed separately as well as a weighted average comparator. Costs associated with the WHO will be assessed by expenditure category (i.e. salaries, overheads, consumables) with economic data collected using a logbook; all other healthcare costs will be assessed by incidence category (i.e. who bears the cost) using available information from sources such as the Medical Benefit Schedule and Pharmaceutical Benefit Scheme. Sensitivity/uncertainty analyses will be undertaken to investigate the robustness of the ICERs to variations in key cost, pathway and outcome parameters in the trial and across sites.

### Data collection methods for child-participants who exit prematurely

Children may exit prematurely from the study because of voluntary withdrawal or termination of WHO intervention due to harm (e.g. allergic reaction to materials). Participant retention will be supported within the study through provision of routine follow-up and regular feedback on child progress via the TherApp summary report that can be generated by parents throughout the trial. Where possible, all children will be followed to the study end point (3 years) so that data are available for analyses. Lack of adherence to the treatment plan will be recorded using TherApp and will not constitute a reason for withdrawal. Reasons for withdrawal from the intervention, or the study, will be recorded to assist with management of missing data and interpretation of results.

### Monitoring of harm and adverse events

No harm or adverse events from orthoses are reported in the literature but are occasionally noted in clinical practice; these are temporary and non-sentinel. Harm arising from the WHO could include the development of pressure areas on the skin, pain, disturbed sleep or behaviour, and skin allergies from specific splint materials while wearing the orthosis, and heat during orthosis fabrication. Children in both groups are at risk of a reduction in joint range of movement as part of the natural course of CP during growth and development. Adverse events unrelated to the study may also occur and will be adjudicated by the Data Monitoring Committee. Data related to harm and/or adverse events for all children will be collected throughout the study by the therapist who manufactures the WHO (routine follow up), retrospectively by study research assistants (6 monthly) and via TherApp alerts. If the TherApp registers an adverse event an automated email alert to the study research assistant will enable appropriate follow up.

### Data management

Data will be collected using a combination of paper-based and web-based data forms supported by the secure Research Electronic Data capture (REDCap) data management system [39] hosted at the Murdoch Childrens Research Institute. REDCap supports quality control measures including rule-based data entry to reduce data entry errors. In addition, data cleaning will be undertaken. Secure electronic data storage will be undertaken using REDCap, and secure (locked) local storage of original paper-based versions of data collected will occur in accordance with ethically approved procedures for each trial site. Participants will be assigned identification codes on enrolment to the study. These codes will be used during data entry so that data are de-identified during analyses and only aggregated data reported to protect the privacy of participants.

### Statistical methods

The primary analysis will be by intention to treat. Comparison between the intervention and the control groups in the difference from baseline in the passive range of wrist extension (primary outcome) will be presented as the mean difference between the groups and its 95 % confidence interval, obtained using linear regression adjusted for the stratification factors of site and range of passive wrist extension at baseline. The regression model will be fitted using generalised estimating equations (GEE) to allow for the clustering of observations within children for those with both limbs in the study. To explore the effect of the adherence to WHO wearing schedule (i.e. a dose response relationship), a linear regression model will be fitted with compliance to treatment as a predictor and difference in the passive range of wrist extension from baseline to 36 months as the outcome, applied to all study participants. Again this model will be fitted using GEEs to allow for the clustering of limbs within participants. Evidence for an interaction between age and treatment, and between severity (Neurological Hand Deformity Classification) and treatment, will be explored by the inclusion of interaction terms in the linear regression models as well as GEE models. The analyses will be repeated, adjusting for potential confounders including occasions of upper limb BoNT-A injections and frequency of upper limb intervention. Analysis will also be undertaken using the ‘per protocol’ population excluding children who received surgical intervention or casting during the study. All data available from children who are withdrawn from the study prior to study completion will be used for analysis. Imputation of missing data will only be considered in the primary analysis if less than 10–20 % of the primary outcome is missing and will be undertaken throughout multiple imputation models.

Depending on whether data are continuous, categorical or dichotomous, the appropriate generalized linear model will be used to estimate the effect of treatment across the study period on secondary outcomes, again fitted using generalised estimating equations. All analyses will be adjusted for the same stratification factors as for the primary analysis and carried out on intention to treat and per protocol populations.

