### Sample size

Sample size calculations were performed according to the primary dependent variable: passive range of movement of wrist extension (measured with fingers extended) at 3 years. Sample size calculations were based on data provided by Rameckers et al. [26] who reported a baseline standard deviation (SD) of 12.4° of passive wrist extension in a group with hemiplegic CP. Rameckers et al. [26] included a more homogeneous group of children than we intend and, therefore, in the absence of clear evidence in the literature, the variability has been estimated to approximate 22° (10° greater than Rameckers et al.’s more homogenous group). Based on a SD of 22° for the primary outcome, 77 participants per group would be required to detect a 10° between-group difference in passive range of movement at 36 months with 80 % power and a two-tailed level of significance of 0.05. A 10° difference was chosen as differences greater than 5 to 10° of movement are deemed clinically important [21]. We used data from our previous successfully completed RCTs of upper limb interventions for children with CP to estimate withdrawal and loss-to-follow-up rates. Prior withdrawal rates ranged from 0 to 10 %, with an additional loss-to-follow up in these RCTs ranging from 0 to 3 % over periods of 6 months. We anticipate that loss-to-follow up in this 3 year study will be higher than 3 %, and thus estimate a 10 % loss. Consequently we predict a combined withdrawal/loss-to-follow-up rate of 20 %. Based on these estimates, we aim to recruit 194 children. Of note, children may have both limbs included in the study. The presence of two limbs was not included in the sample estimates but will be used in the analyses. Including both limbs will increase study power; hence the sample size is expected to be conservative if two limbs are included for some children. Randomised trial experience in Australia suggests we will require at least 12 months to recruit the required sample.

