### Randomisation

Once consent and assent (for those children aged 12 years or more) has been obtained by the research assistant, and following baseline assessment, children will be randomised to either the treatment or comparison group with an allocation ratio of 1:1, using a web-based randomisation procedure to ensure concealed allocation. Randomisation will be completed using randomly permuted blocks of variable length, stratified by study centre (5 strata), and by passive wrist range of movement (3 strata: wrist extension >0° (fingers extended); wrist extension between −45°-0° (fingers extended); or wrist extension < -45° (with or without finger extension)). For children with bilateral involvement, where both limbs meet inclusion criteria, both limbs will be allocated to the same intervention based on the randomisation sequence and stratification will be based on the passive wrist range of the more involved limb. Data will be collected for both upper limbs and included in the analysis at the end of the study for limb-based outcomes.

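### The primary change-score model adjusts for a three-band baseline range set by the worse limb rather than each limb's own baseline angle, and the sample size uses the SD of a final value

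*Protocol article*

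**What the plan says.** Statistical methods (Protocol article) defines the primary comparison as the between-group mean difference in change from baseline, "obtained using linear regression adjusted for the stratification factors of site and range of passive wrist extension at baseline". It is fitted by GEE to allow for two limbs in one child.

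Randomisation defines the range factor as three bands: above 0°, −45° to 0°, and below −45°. Where both limbs qualify, "stratification will be based on the passive wrist range of the more involved limb". Both limbs receive the same allocation and both enter the limb-based analyses.

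Sample size is calculated for range at 3 years: "Based on a SD of 22° for the primary outcome, 77 participants per group would be required to detect a 10° between-group difference", with 80% power and "a two-tailed level of significance of 0.05". The 22° is a baseline SD of 12.4° from a more homogeneous published group, raised by about 10°. Second limbs are not counted, and the section calls the sample size conservative for that reason. It gives neither an SD of change nor a correlation between the baseline and 36-month angles.

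**The concern.** Two features of the plan do not fit together well.

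First, a change score carries baseline variation into the outcome, and the covariate meant to remove it is coarse. Two limbs 40° apart can share the band above 0°. In a bilateral child, the less involved limb is adjusted for an angle measured on the other arm, although its own angle is recorded at baseline.

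Second, the trial is sized on one quantity and analysed on another. The SD of change equals the SD of the final value only when r = 0.5; below that it is larger. Because r is not stated, a reader cannot tell what power the planned model has.

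What is at stake is precision, not validity: some power that data already collected would recover.

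**Working it through.** **Inputs from the Protocol article (Sample size, Randomisation).** Difference 10°, SD 22°, two-sided 0.05, 80% power, 20% loss, 1:1 allocation, cut-points at 0° and −45°.

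**Assumptions, not in the document.** The baseline and 36-month SDs are both 22°, baseline angles are normal with mean −10° to +30°, r runs from 0.3 to 0.7, and there is one limb per child. Site effects are ignored.

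**1. The plan's own figure.** The normal approximation gives 2 × (1.96 + 0.8416)² × 22² / 10² = 75.98, so 76 per group. With the noncentral t, power is 79.5% at 76 and 80.03% at 77, so 77 reproduces. Then 77 / 0.80 = 96.25, which rounds up to 97 per group, or 194. The figure is correct for a comparison of final values with SD 22°.

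**2. Residual SD under each model.**
- Unadjusted change: 22 × √(2(1 − r)).
- Change with bands: 22 × √((1 − r)²(1 − R²) + 1 − r²), where R² is the share of baseline variance that the bands explain.
- Change with the limb's continuous baseline: 22 × √(1 − r²).

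**3. R² for these cut-points.** It is 0.72 at a baseline mean of −10°, 0.69 at 0°, 0.61 at +10°, 0.47 at +20° and 0.32 at +30°.

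**4. Example at r = 0.3.** The standard error is SD × √(2/77) = SD × 0.161.
- Bands, mean +30°: 22 × √(0.49 × 0.685 + 0.91) = 24.6°, power 71%.
- Bands, mean −10°: 22 × √(0.49 × 0.276 + 0.91) = 22.5°, power 78%.
- Continuous baseline: 22 × √0.91 = 21.0°, power 84%.

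**5. Power at 77 per group** (range over baseline means −10° to +30°):

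| r | Bands, as planned | Each limb's continuous baseline |
|---|---|---|
| 0.3 | 71–78% | 84% |
| 0.5 | 83–87% | 90% |
| 0.7 | 96–97% | 97.5% |

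Over this range the residual variance is 5–37% larger with bands.

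**6. Where planned power crosses 80%.** Setting the banded residual SD equal to 22° gives r = s / (1 + s), with s = √(1 − R²). For R² = 0.724, s = 0.525 and r = 0.34. For R² = 0.315, s = 0.828 and r = 0.45. If the bands explained only 10%, r would be 0.49. Above the relevant value, planned power exceeds 80%. With the continuous baseline the residual SD is at most 22° for every r ≥ 0, so power is at least 80%, provided that the 36-month SD is 22°.

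**7. Bilateral children.** A simulation of 154 children took 40% as bilateral, a within-child limb correlation of 0.5, worse-limb bands and cluster-robust standard errors (1,500 runs per scenario):

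| Baseline mean | r | Bands | Bands plus limb's own baseline |
|---|---|---|---|
| 0° | 0.3 | 81% | 86% |
| 0° | 0.7 | 98% | 98% |
| +30° | 0.3 | 73% | 85% |
| +30° | 0.5 | 88% | 93% |
| +30° | 0.7 | 97% | 99% |

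The direction is the same. Second limbs add some power under either model in most scenarios.

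**The case against.** The strongest reply is that Statistical methods never says three categories, and that the worse-limb rule is written for randomisation. If baseline range enters as each limb's measured angle, change adjusted for baseline gives the same treatment estimate as the model proposed here, and the efficiency point disappears. Covariate coding is also often left to an analysis plan. This stands in part: the wording allows that reading. But the sentence calls the covariates stratification factors, and the only range factor so defined has three bands. If the measured angle is meant, the sentence still needs to say so.

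The second reply is that power may be ample. At r = 0.5 the planned model already exceeds 80%, at r = 0.7 the gain is about one point, and second limbs are not counted in the sample size. All of this stands, and it limits the size of the point.

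A reader might also infer that secondary outcomes go without their own baselines, since "All analyses will be adjusted for the same stratification factors as for the primary analysis". That sentence says what is included. It does not exclude an outcome's own baseline value, so this would be an argument from silence.

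**Conclusion.** The point holds as one of efficiency and of clarity about the SD. On the natural reading, the planned model is unbiased under randomisation but gives up about 5–13 points of power at r = 0.3, 3–7 at r = 0.5 and about 1 at r = 0.7, compared with adjusting for each limb's own baseline angle. These figures depend on the assumed r, baseline mean and equal SDs, none of which the document supplies.

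Three stronger conclusions are tempting and are not supported:
- **That the trial misses 80% power.** The sample size reproduces. Under these assumptions planned power falls short only if r is below about 0.34–0.45 (0.49 if the bands explain very little), and the document gives no r.
- **That the bands leave most of the baseline variation in the residual.** They explain more than half of it unless the baseline mean exceeds about +18°.
- **That a continuous baseline guarantees 80%.** It does so only if the 36-month SD really is 22°, which Sample size presents as an estimate made without clear evidence.

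**What to change.** In Statistical methods, name each limb's own continuous baseline passive wrist extension as a covariate in the primary GEE model, and keep site and the randomisation stratum. With that covariate, analysing change or the 36-month value gives the same treatment estimate.

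In Sample size, state that 22° is the SD of the 36-month value before baseline adjustment.

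Optionally, adjust each secondary outcome for its own baseline value where one is collected.

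The cost is one covariate in the model statement and one sentence on the SD. No new data are needed and the recruitment target does not change. The change should be made before anyone sees outcomes by group.
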